### Oversight and monitoring

**
*Composition of the coordinating center and trial steering committee*
**

The Trial Management Group (TMG) will oversee the daily execution of the trial, while the Trial Steering Committee (TSC) will offer supervision. The TMG will include the principal investigator, research assistants (RAs), the Intervention Coordinator (IC), yoga instructors, and a representative of
*Sahayoginis*.

There will be six members in the TSC and one of them will be a woman who has recently delivered a baby. She will represent patient perspectives and ensure that the safety of the participants is prioritized throughout the implementation of the trial. Two independent researchers will co-chair TSC. Details about the membership, roles and responsibilities, and TSC meetings are provided in the supplementary file (
*Extended Data*
^
36
^). Representatives from the TMG will participate in the TSC meetings.

**
*Composition of the data monitoring committee, its role and reporting structure*
**

Due to the nature of the trial and the low risk for participants, the TSC will also take on the role of the data monitoring committee. The Clinical Research Coordinator will submit a report every two weeks summarizing SAEs in both the arms without removing the blinding. During the TSC meetings, data related to trial progress and participants' safety will be reviewed and discussed.

**
*Adverse event reporting and harms*
**

The IC and yoga instructors will be trained to identify Serious Adverse Events (SAEs) and notify them to the CRC. CRC will maintain a log of all the following SAEs in both arms.

1)Death due to any cause2)Hospitalization due to any cause3)Suicide attempt4)Spontaneous abortion or stillbirth

RAs will independently document SAEs at the three-month and post-delivery follow-up assessment. PI will submit an initial report to the Institutional Ethics Committee about the SAE (related or unrelated) within 24 hours of becoming aware. This will be followed up by a detailed analysis report submitted to the Institutional Ethics Committee within 14 days of the knowledge of the occurrence of the SAE. A standard operating procedure will include all the details about the detection, appropriate response, and reporting of SAEs. If any SAE requires an immediate response, an independent medical specialist will do so within two working days. A summary of all serious adverse events will be sent to the Institutional Ethics Committee, the funder, and the TSC regularly as part of the progress report. If there is a statistically significant difference in prevalence of SAEs in the two arms of the trial, the TSC will take a decision to unblind the data. All necessary and appropriate medical assistance will be provided to participants in the PIMS for injuries related to participation in the trial (intervention arm). There will be no financial burden on the participants for trial-related injuries and adverse events.

**
*Frequency and plans for auditing trial conduct*
**

The sponsor and the Institutional Ethics Committee will monitor the aspects of the study on an ongoing basis. PI will send a monthly progress report to the Institutional Ethics Committee.

**
*Plans for communicating important protocol amendments to relevant parties (e.g., trial participants, ethical committees)*
**

During the progress of the trial, we may have to undertake certain modifications in the protocol that may affect the scientific value of the study, participant safety, or how the study is conducted. PI will first submit these modifications to the Institutional Ethics Committee as amendments to the protocol and then seek approval from the TSC and the sponsor. We will communicate all the changes made to the protocol to the trial participants through written communication. The final report submitted to the funder will enlist all the amendments to the protocol.

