### Objectives

The overall aim of this pilot randomized controlled trial is to examine the feasibility, acceptability, and preliminary efficacy of Yoga-Sanskar (YS), a yoga-based intervention to improve antenatal depression.

The primary objectives of this pilot randomized trial are:

1. To estimate participant eligibility, recruitment and retention-in-care and study completion rates.

2. To assess the feasibility of delivering Yoga-Sanskar intervention and acceptability of this intervention by the participants.

3. To assess the adherence rate, safety, and preliminary efficacy of Yoga-Sanskar intervention in improving antenatal depression (primary outcome).

The secondary objectives of this pilot randomized trial are:

1. To assess the preliminary efficacy of Yoga-Sanskar intervention on anxiety, stress, and quality of life (secondary outcomes) during pregnancy.

2. To assess the preliminary efficacy of the intervention on pregnancy outcomes (preterm labor, type of delivery, birthweight, and post-partum depression.

3. To explore the feasibility of administering all the evaluation tools including the Client Service Receipt Inventory to assess the healthcare and intervention costs.

4. To explore the feasibility of following up recruited participants four weeks post-delivery.

5. To study the psychometric properties of the translated versions of the Pregnancy Experience Scale, Common Symptoms in Pregnancy inventory, Attitude towards Yoga during Pregnancy scale, and the Five Facet Mindfulness Questionnaire.

**
*Trial design*
**

Single-blind individual randomized parallel group-controlled pilot trial with 1:1 allocation ratio.

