If there is spontaneous abortion or stillbirth, participation in both arms will be discontinued. Other than this, there are no specific criteria to discontinue the intervention. A few modifications in the sequence for individual participants may be made by the yoga instructor based on feedback from them. Obstetricians may advise participants to discontinue yoga due to health issues, or they may decide to stop practicing yoga themselves for any reason.

**
*Strategies to improve adherence to interventions*
**

The IC, yoga instructors, and
*Sahayoginis* will regularly contact participants in the YS arm to motivate them to practice yoga at home regularly. Adherence to home practice will be assessed using the yoga journal. We expect
*Sahayoginis* to contact participants at their homes at least once a week. They will also contact participants in the EUC arm at least once a week by phone. This will help reduce attentional bias.

**
*Relevant concomitant care permitted or prohibited during the trial*
**

Participants will receive usual care throughout the trial, and no specific component of antenatal care or other health services will be prohibited.

**
*Provisions for post-trial care*
**

Participants in both arms will receive information about yoga sessions they can join after the end of the trial. Participation in yoga sessions post-trial will be entirely voluntary. No compensation will be provided to participants who suffer non-negligent harm from trial participation.

**
*Outcomes*
**

We will assess the feasibility and acceptability of the Yoga-Sanskar (YS) intervention and the preliminary efficacy of the intervention on depression in pregnant women.

Process data will inform the feasibility of the enrolment, engagement with the intervention, and completion of the intervention. The process indicators are as follows:

1.Number and proportion of eligible participants enrolled per week in the YS and the EUC arm.2.Number and proportion of enrolled participants in the YS arm who attend the first session, three follow-up training sessions, and the final assessment session.3.Number and proportion of enrolled participants in both arms who complete the follow-up assessment three months post-randomization.

Additionally, we will assess the feasibility of following up with participants until delivery and conducting all the assessments four weeks after delivery.

RAs in the trial evaluation team will maintain the study enrollment logs, and the IC and

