*Sahayoginis* will maintain the intervention delivery log. The logs will be in paper format, and at the end of every week, RAs and IC will enter all the data on an access-restricted computer. We will save the data in password-protected CSV files. Process data for feasibility assessment will be obtained from the above logs.

Trial participants will complete a structured satisfaction survey at the end of the training and the final assessment sessions. We will conduct In-Depth Interviews with trial participants and yoga instructors. These interviews will focus on the intervention’s delivery, content, comfort, and complexity. We plan to enroll around 20 participants (12-13 from the YS arm and 7-8 from the EUC arm). However, data saturation will determine the final sample size for the qualitative study. Quantitative data obtained from the satisfaction survey (details below) and qualitative data from the IDIs will inform the acceptability of the intervention.

The description of measures that will be used to assess the preliminary efficacy of the intervention is given in
Table 2.

**Table 2. T2:** Measures to assess the preliminary efficacy.

Outcome	Measure	Time-point
Depression	Patient Health Questionnaire-9	Baseline, One, two, and three-months post-randomization, and post-delivery
Anxiety	Generalized Anxiety Disorder-7	Baseline, three-months post-randomization, and post-delivery
Stress	Perceived Stress Scale (PSS)	Baseline, three-months post-randomization, and post-delivery
Quality of Life	EuroQoL 5 Dimensions Score (EQ-5D-5L)	Baseline, three-months post-randomization, and post-delivery
Minor ailments in pregnancy	Common Symptoms in Pregnancy (CSIP)	Baseline, three-months post-randomization, and post-delivery
Experience of pregnancy	Pregnancy Experience Scale	Baseline, three-months post-randomization, and post-delivery
Attitude	Attitude towards Yoga practice during pregnancy scale	Baseline, three-months post-randomization, and post-delivery
Treatment Expectation	Credibility Expectancy Questionnaire	Three to four weeks post-randomization
Self-Efficacy	Yoga Sequence Self-Efficacy Assessment Yoga Practice Self-Efficacy Assessment	Three to four weeks post-randomization
Competence	Yoga Performance Assessment Scale Online Structured Competency Assessment	Three to four weeks post-randomization
Awareness	Five Facet Mindfulness Questionnaire	Baseline, three-months post-randomization, and post-delivery

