### Assignment of interventions: allocation

**
*Sequence generation*
**

Serially numbered, opaque, sealed envelopes (SNOSE) will be used for treatment allocation. Clinical Research Coordinator (CRC) based in the Directorate of Research, PIMS will prepare SNOSE using the randomization list created by the trial statistician who will independently generate the randomization list using the statistical program
R (version 3.6.1). First, a list of variable block sizes (randomly selected block sizes of 2/4/6/8) will be created, followed by a list of intervention allocation (YS or EUC) using a 1:1 allocation ratio. CRC and trial statistician will be independent of the study team and will not interact with the RAs or the IC.

**
*Allocation concealment mechanism*
**

The IC will randomly allocate participants to the intervention group using SNOSE after they complete their baseline assessment.

**
*Implementation*
**

The IC will collect a set of opaque sealed envelopes from CRC as per the serial numbers a few hours before the recruitment. The IC will open the opaque sealed envelopes (as per the serial numbers) in front of the participants and immediately inform them about the intervention group (i.e., YS or EUC) assigned to them. Participants will be asked to keep their group assignment private from the RAs at the three-month follow-up, and post-delivery assessments. To maintain allocation concealment, neither the RAs nor any staff working at the hospital will have access to the randomization lists. The IC will inform the CRC of the unique identification number of the participant (and no other details) and the intervention allocation group. The CRC will maintain the record of intervention allocation.

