### Assignment of interventions: blinding

**
*Who will be blinded?*
**

Participants, their family members, and study team members involved with intervention delivery (IC and yoga instructors) will be aware of participants’ assigned intervention during the trial. It is not possible to avoid bias arising due to this. RAs will complete baseline, three-month follow-up, and post-delivery assessments, and they will not interact in any way with the intervention team. RAs will not be aware of the intervention allocation status. Participants and family members will be instructed not to disclose whether they are receiving YS intervention or EUC to the RAs at the time of the follow-up assessments. Additionally, RAs will also remind participants not to reveal their group assignment to them so that they remain blind to the participant’s treatment allocation.

Obstetricians will not be aware of the intervention allocation status, minimizing the risk of any change in their behavior while dealing with the participants.

The intervention team led by the IC and the outcome assessment team comprising RAs will not have any interactions during the trial. They will work independently of each other in separate locations and will have no communication about trial participants and their intervention allocation status. During the training of RAs in the outcome assessment team, particular emphasis will be given to explaining the equipoise between the two interventions.

We will monitor the risk of contamination at the level of the yoga instructors, intervention coordinator, and participants. Yoga instructors and the intervention coordinator will be requested not to share the information about YS with pregnant women other than those enrolled in the intervention arm. They will also ensure that participants in both the arms adhere to the group randomly allocated to them.

**
*Procedure for unblinding if needed*
**

If there is any yoga-related adverse event, we will reveal the intervention group allocation to the obstetrician.

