### Data collection and management

**
*Plans for assessment and collection of outcomes*
**

Research Assistants (RAs) will utilize Case Record Forms (CRF) to gather information during the initial assessment and the three-month follow-up. Data collection will be conducted using pen and paper, with subsequent manual entry into Microsoft Excel for digital conversion. The data will be stored as a CSV file, with original timestamps for entries and a record of any subsequent modifications in an audit trail. Documentation concerning the fidelity and quality of yoga intervention delivery will follow a similar process, with data stored in CSV format. Qualitative data will be recorded using digital voice recorders, and accompanying memos and field notes will be transcribed from Marathi to English for analysis. Data will be anonymized but associated with the trial ID.

The Clinical Research Coordinator (CRC) will conduct weekly checks on each data source for accuracy, consistency, and completeness, promptly addressing any queries and updating the database while maintaining an audit trail. Initially, separate databases will house distinct data types, with consolidation into a master database upon completion of data collection. Password protection will safeguard the data, with exclusive access granted to the CRC and no other trial team members.

**
*Plans to promote participant retention and complete follow-up*
**

During the initial assessment, RAs will inform the participants about the date for the three-month follow-up evaluation. RAs will call the participants one week before the follow-up assessment to remind them about the assessment. If the participant is traveling or is unavailable for any reason, there will be a seven-day window following the due date to complete the assessment. The assessments will be conducted preferably at the health center or Anganwadi center. If the participant is unable to come there, then the RA will complete the assessment at participant’s home.

**
*Data management*
**

We will prepare a Trial Master File that will encompass all vital documents. Documentation pertinent to the trial will be preserved for seven years following its conclusion. After this period, paper-based data will be securely disposed of, while electronic data will be purged of identifiable information.

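### The protocol rests assessor blinding on complete separation from the intervention team, then seats both on one Trial Management Group, so the stated safeguard contradicts itself

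*Protocol article*

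**What the plan says.** Under Objectives (Trial design), the article describes a "Single-blind individual randomized parallel group-controlled pilot trial with 1:1 allocation ratio".

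Under Assignment of interventions: blinding, it names those who are not blinded: participants, their families, and "study team members involved with intervention delivery (IC and yoga instructors) will be aware of participants’ assigned intervention during the trial". The RAs, who carry out the baseline, three-month and post-delivery assessments, are to stay unaware of allocation. The safeguard is stated in absolute terms: "The intervention team led by the IC and the outcome assessment team comprising RAs will not have any interactions during the trial". The same section places the two teams in different locations and bars communication about participants or their allocation. The Recruitment section adds that the IC works independently of the RAs.

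Under Oversight and monitoring, the Trial Management Group (TMG) runs the trial day to day. Its membership reads: "The TMG will include the principal investigator, research assistants (RAs), the Intervention Coordinator (IC), yoga instructors, and a representative of" the Sahayoginis.

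Three other places bear on the same point:

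- **Process data (Interventions, Outcomes).** RAs keep the enrolment logs, while a log of what was delivered is kept by the IC and Sahayoginis. Entry is described as follows: "The logs will be in paper format, and at the end of every week, RAs and IC will enter all the data". The computer used has restricted access. The first process indicator is "Number and proportion of eligible participants enrolled per week in the YS and the EUC arm".
- **Sequence generation.** "CRC and trial statistician will be independent of the study team and will not interact with the RAs or the IC".
- **Retention plans (Data collection and management).** "During the initial assessment, RAs will inform the participants about the date for the three-month follow-up evaluation".

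**The concern.** The RAs administer the questionnaire that holds the primary efficacy outcome, the PHQ-9, and they independently document serious adverse events at follow-up. Obstetricians are also kept unaware of allocation, but they do not collect the PHQ-9. For RA-collected outcomes, the RAs' ignorance of the arm is the blinding that counts.

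On the TMG the RAs would sit with the IC, who opens every allocation envelope, with the yoga instructors, who teach only the yoga arm, and with a representative of the Sahayoginis, who contact yoga-arm women at home and control women by phone. Ordinary business about session attendance, home practice or injuries could reveal who is in which arm. If that happened, knowledge of allocation could colour how the questionnaire is administered and how events are recorded. The reported blinding would then rest on a separation that the protocol itself did not require its staff to keep.

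**Working it through.** No arithmetic applies to the main point. It is settled by setting the statements side by side.

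**1. Separation against shared membership.**

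| Section | RAs and intervention team |
|---|---|
| Recruitment | IC works independently of the RAs |
| Blinding | No interaction of any kind; separate locations; no communication about participants or allocation |
| Oversight and monitoring | RAs, IC, yoga instructors and a Sahayogini representative are members of one group overseeing daily conduct |

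Members of a group that manages the trial day to day interact. The ban in the blinding section covers all interaction, not only talk of allocation, so shared membership breaches it even if allocation is never mentioned. The article states no split meeting, recusal or restricted agenda. This is a direct contradiction.

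**2. Weekly log entry.** The text names RAs and IC as the people who enter the data, immediately after giving each their own log. It does not say that they work together or see each other's entries. The delivery log identifies yoga-arm women, and no separate access rights are stated for the two logs. The data-collection section gives database access to the CRC alone. That suggests an intention to restrict access, but it does not explain how RAs and IC then enter the logs. This is a possible leak that needs clarifying.

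**3. Enrolment by arm.** The first process indicator is split by arm, and process data are said to come from the logs, one of which the RAs keep. Read literally, this could put arm into an RA-kept log. It need not: the Implementation paragraph has the CRC keep the allocation record, so arm can be linked by participant number without the RAs. This too is a possible leak only.

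**4. The CRC sentence.** Sequence generation bars the CRC from interacting with the RAs or the IC. The Implementation paragraph of the same allocation section has the IC collect envelopes from the CRC and report each allocation back. The sentence cannot stand as written. The conflict concerns the IC, however, and does not show that RA blinding fails.

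**5. The follow-up date.**

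- RAs give the three-month date at the initial assessment.
- Randomisation follows about a week later (Recruitment).
- Table 2 counts three months from randomisation.
- If the date were counted from baseline, it would fall about 7 days early. The whole permitted window is 7 days after the due date, so the offset would be about as large as the window.
- The article does not say from which day the RAs count, and they may add the planned week. Any shift would affect both arms alike.

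This is a minor ambiguity, separate from blinding.

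**The case against.** The strongest reply is that membership of a committee is not disclosure. The oversight section lists who belongs to the TMG. It does not say that individual allocations are discussed there, and the blinding section forbids such discussion. How the meetings run is the kind of detail an article may leave to a fuller protocol. Other protections of assessor blinding also remain: participants and families are told not to disclose, RAs remind them, and RAs are trained on equipoise. This is a pilot whose leading objectives are feasibility and acceptability, with only preliminary efficacy.

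Much of this stands. A reader might infer that every woman's allocation is bound to reach the RAs, or that the single-blind label is false. The documents do not support either: shared membership makes exposure possible, not certain. A reader might also infer from the data-entry sentence that RAs and IC enter data jointly, but it is equally consistent with each entering their own log.

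The reply does not remove the contradiction. The article did not leave the matter open. It stated an absolute rule of no interaction and then a membership list that breaks it. Instructions to participants guard against a different route of disclosure, not contact among staff.

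**Conclusion.** The point holds as an internal contradiction. The separation that the protocol offers as the basis of assessor blinding cannot be followed together with the stated TMG membership. RA unblinding is a plausible result, not an established one. What is at stake is the credibility of the RA-collected outcomes, above all the PHQ-9.

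The size of any bias cannot be computed from the document. It would be tempting to set it against the standardised effect of 0.2 in the Sample size section, but that figure serves only to size the pilot and says nothing about assessor bias.

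The log entry and the by-arm indicator are ambiguities that could open further leaks. The CRC sentence is a real wording conflict, and the follow-up date a minor ambiguity; neither shows that blinding fails.

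The conclusion assumes that the TMG meets as one group, since nothing in the article says otherwise. A documented barrier in the full protocol would answer the main point, though the article's wording would still need reconciling.

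**What to change.** 1. Remove the RAs from the TMG. Alternatively, limit them to separate sessions without intervention staff, allocation information or participant-level delivery content, and reword the blinding section to match.
2. State that RAs enter only the enrolment log, which carries no arm, and that the IC and Sahayoginis enter only the delivery log, each in files the other side cannot open.
3. Have the CRC add arm to the weekly enrolment counts from its allocation record.
4. Correct the sentence barring CRC contact so that it allows the envelope and allocation-reporting steps already described. Allow the CRC to pass the RAs two items only: participant number and a three-month due date counted from randomisation.

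The cost is revised wording in the allocation, blinding, outcomes, data-collection and oversight sections, plus a small relay task for the CRC. No participants or visits are added.

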Improvement in self-awareness/mindfulness is proposed as a potential mechanism of action through which a yoga-based intervention improves mental health outcomes/depression
^
13
^. The training during yoga sessions will focus on improving self-awareness/mindfulness, as the increase in mindfulness is associated with decreased distress and other psychological symptoms. We will use a 17-item Five-Facet Mindfulness Questionnaire that measures five aspects: non-reactivity to inner experience, observing, acting with awareness, describing with words, and non-judging of experience. The original English version of the scale
^
34
^ is translated into Marathi and is included in the supplementary file (
*Extended Data*
^
17
^).

**
*Pregnancy outcomes*
**

We will gather information about the outcome of pregnancy (normal birth/stillbirth), whether the delivery took place at-term, and the birthweight of newborn based on the hospital records.

**
*Self-report log*
**

Participants in both arms will document any injuries or non-serious adverse events during the trial in the yoga journal (and a similar journal will be given to the participants in the EUC arm). IC and
*Sahayoginis* will keep track of this and report to the CRC in case of adverse events.

**
*Economic evaluation*
**

In the future explanatory trial, we plan to assess the cost-effectiveness of the YS intervention relative to the EUC. Effectiveness/health outcomes will be estimated using the Quality Adjusted Life Years based on the EQ-5D-5L data collected at the baseline and three months post-randomization. Costs will comprise intervention costs, healthcare resource costs, and wage loss costs. In this pilot trial, we will explore the feasibility of using the Client Service Receipt Inventory to estimate healthcare resource costs and wage loss costs. Intervention costs will be estimated using the trial records.

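### Between assessment visits, serious adverse events are looked for more intensively in the yoga arm than in the control arm, so the between-arm comparison may be biased

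*Protocol article*

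**What the plan says.** The section on adverse event reporting and harms names the people who feed the running SAE record: "The IC and yoga instructors will be trained to identify Serious Adverse Events (SAEs) and notify them to the CRC". The Clinical Research Coordinator (CRC) then keeps the record for the whole trial: "CRC will maintain a log of all the following SAEs in both arms". The listed events are death, hospitalisation, suicide attempt, and spontaneous abortion or stillbirth. A second route is the blinded research assistants (RAs): "RAs will independently document SAEs at the three-month and post-delivery follow-up assessment". Table 2 schedules the SAE report form at baseline, three months and post-delivery. The same section defers details of SAE detection to a standard operating procedure, which is not shown.

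On contact between visits, the adherence section expects Sahayoginis "to contact participants at their homes at least once a week" in the YS arm. For the control arm it says: "They will also contact participants in the EUC arm at least once a week by phone". The reason given for these calls is to limit attentional bias.

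On non-serious harms, the self-report log covers everyone: "Participants in both arms will document any injuries or non-serious adverse events during the trial in the yoga journal". Control women get a comparable booklet of their own. The duty to follow these entries up is not limited to one arm: the IC and Sahayoginis "will keep track of this and report to the CRC in case of adverse events".

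The comparison is used in two ways. Every two weeks the CRC reports a summary of SAEs in both arms to the Trial Steering Committee (TSC). A statistically significant difference in SAE prevalence between the arms leads to a TSC decision to unblind the data.

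**The concern.** Safety is part of the third primary objective, and the protocol attaches an action to a difference in SAEs between the arms. Such a difference is interpretable only if events are sought in the same way in both arms.

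Between RA visits they are not. The trained staff have repeated planned contact with YS women and little with EUC women. The only people who contact EUC women every week are not on the training list, and the protocol does not say that they ask about SAEs. These staff also know the allocation.

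Two things are at stake. First, with equal true risk, YS could show more logged events simply because more of them are found. Second, an EUC hospitalisation or suicide attempt could reach the CRC late. The 24-hour report to the ethics committee runs from awareness, so late detection also means late reporting.

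**Working it through.** The protocol gives no figure for detection, so there is none to reproduce. The point rests on comparing the routes, and the numbers below only show scale.

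**1. Routes shared by both arms**
- A journal for injuries and non-serious events, with the same named trackers (self-report log).
- Sahayogini contact at least weekly, at home in YS and by telephone in EUC (adherence section).
- Weekly symptom reporting (minor ailments section).
- SAE documentation by blinded RAs at three months and post-delivery.

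**2. Routes only or mainly in YS**
- Instructors trained to identify SAEs, who teach only the YS arm.
- A safety checklist at supervised sessions, signed off by the instructor.
- Weekly group sessions.
- Regular contact from the IC and instructors. EUC women have a single education session with the IC, plus the meeting at which the IC opens the envelope.

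**3. Scheduled contacts with SAE-trained staff over about 13 weeks**
- YS supervised sessions: 1 + 3 + 1 = 5 (first session, three follow-up sessions, competency session).
- YS weekly groups: 9 if held in weeks 5 to 13, or 12 if held in weeks 2 to 13. That instructors lead them is an inference.
- YS total: 5 + 9 = 14 to 5 + 12 = 17. If instructors do not lead the weekly groups, 5. The Discussion counts only three supervised sessions, which would lower each figure by two.
- EUC: 1 intervention session.

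**4. All scheduled contacts, trained or not (groups from week 5)**
- YS: 5 supervised + 9 groups + 13 home contacts + 1 RA visit = 28.
- EUC: 1 session + 13 calls + 1 RA visit = 15.
- The planned gap between EUC contacts is therefore about one week. The large imbalance is in trained contact.

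**5. What unequal detection would do (assumed rates)**

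With the same true risk in both arms, apparent risk ratio = 1 / d, where d is EUC detection relative to YS. With 25 women per arm, a true risk of 20% and full detection in YS, expected YS events are 25 × 0.20 = 5.0. Expected EUC events are:
- d = 0.9: 5.0 × 0.9 = 4.5, ratio 1.11
- d = 0.7: 5.0 × 0.7 = 3.5, ratio 1.43
- d = 0.5: 5.0 × 0.5 = 2.5, ratio 2.0

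**6. Chance of a false significant difference**

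The protocol names no test for the SAE trigger. With a two-sided Fisher exact test at 0.05 and 25 per arm:
- True risk 20%: 2.2% with equal detection, 4.2% at d = 0.7, 8.6% at d = 0.5.
- True risk 10%: 0.9%, 0.9% and 1.3%.
- With no EUC events, 6 YS events are needed for significance.

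Formal false alarms stay uncommon. The more likely harm is a distorted estimate or a late-detected control event.

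**The case against.** The strongest reply is that the control arm is far from unobserved. EUC women are telephoned at least weekly, keep a journal with the same trackers as in YS, and are asked about SAEs by blinded RAs. The four SAEs are memorable, so the RA visits should recover many that were missed earlier. The unseen operating procedure may already settle who is trained and what is asked.

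Much of this stands, and it rules out three stronger readings that a reader might infer:
- *Control-arm events go unseen for months.* The text does not support this. A delay of that length would need every weekly call and the journal to miss the event.
- *Non-serious harms are sought much harder in YS.* Both arms have a journal and the same reporting route. What remains is home versus telephone contact and the session checklist.
- *The comparison is biased.* The documents show only that it may be.

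The reply does not remove the SAE point. The protocol states who is trained and how EUC women are contacted, and these are choices rather than details left out. The journal as described is for injuries and non-serious events. The RA record is the more even source, but it comes late and is not named as the basis of the comparison. Participation also ends after spontaneous abortion or stillbirth, so RA visits may not follow two of the listed events. That rule applies to both arms, and stillbirth is to be taken from hospital records, but spontaneous abortion is not named there.

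**Conclusion.** The point holds for serious events between RA visits. Detection is more intensive and better trained in YS, so the comparison may lean towards more events in YS, and an EUC event could be found late if the weekly call and journal miss it. The size cannot be derived from the documents: the ratios of 1.11 to 2.0 follow entirely from assumed detection rates and would shrink to the extent that RAs recover missed events. The operating procedure may already cover part of this. In a pilot of 50 women, where the trigger leads to a decision on unblinding and no stopping rule is attached, this should be fixed but is not critical. It is best settled before enrolment, because events missed during the trial cannot reliably be recovered afterwards.

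**What to change.** 1. Include the Sahayoginis in the SAE training. Have them ask the same scripted SAE question at the weekly contact already planned in each arm and report the answers to the CRC. Align the operating procedure with this. The contact mode need not change.
2. State that any between-arm comparison rests on the SAEs collected by the blinded RAs, over the same window in both arms. Include women whose participation ended after abortion or stillbirth, by RA contact or hospital record. List separately the events reported only by instructors or at yoga sessions.

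The cost is a short training item, slightly longer weekly contacts, some follow-up of women whose participation ended, and a few sentences in the safety section. No new staff or visits to the intervention are needed.
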